# Surgical treatment of neuromuscular Early Onset Scoliosis with a bilateral posterior one-way rod compared to the Spring Distraction System: study protocol for a limited-efficacy Randomized Controlled Trial (BiPOWR)

**DOI:** 10.1186/s12891-022-06048-4

**Published:** 2023-01-10

**Keywords:** BiPOWR, Early Onset Scoliosis, Neuromuscular, Growth, Spring Distraction System, SDS, One Way Self-Expanding Rod, OWSER, Pediatric spine, Bipolar technique

## Abstract

**Background:**

Early Onset Scoliosis (EOS) is a progressive spinal deformity in children, and a potentially life-threatening disease. “Growth-friendly” surgical techniques aim to control the deformity, while allowing the spine and trunk to maintain growth. Current “growth-friendly” systems such as the traditional growing rod (TGR) and magnetically controlled growing rod (MCGR) have limitations that reduce their efficacy and cost-effectiveness. Recently, two “growth-friendly” systems have been developed that mitigate many of these limitations, the Spring Distraction System (SDS) and the One Way Self-Expanding Rod (OWSER). The purpose of the multicenter BiPOWR trial is to investigate, describe and compare the 1-year limited-efficacy and -safety of both strategies in the treatment of neuromuscular EOS.

**Methods:**

After informed consent, 28 neuromuscular EOS patients will be randomized to receive either the SDS or the OWSER. Patients and caregivers will be blinded to allocation until after surgery. Primary outcomes will be maintenance of coronal curve correction and the occurrence of serious adverse events. In addition, spinal growth, implant lengthening, and perioperative findings are recorded systematically. At each follow-up moment, the Early Onset Scoliosis Questionnaire (EOSQ-24) will be used to assess health-related quality of life. All outcomes will be compared between groups.

**Discussion:**

The BiPOWR trial is the first randomized controlled trial that compares two specific “growth-friendly” implants in a specified EOS population. It will determine the 1-year limited-efficacy and safety of the SDS and OWSER implants.

**Trial registration:**

Clinicaltrials.gov: NCT04021784 (13–06-2019). CCMO registry: NL64018.041.17 (06–05-2019).

## Background

Early Onset Scoliosis (EOS) is a complex three-dimensional deformity of the spine and trunk, which, if left untreated, can result in severe cardiopulmonary compromise or even death [1, 2]. The early onset of the deformity carries with it a high risk of progression, which places importance on early treatment to preserve pulmonary function. This is even more important in patients with neuromuscular diseases such as spinal muscular atrophy or Duchenne muscular dystrophy. In these patients, respiratory muscles that are necessary for normal in- and expiration weaken, which, together with altered chest wall compliance, leads to further respiratory compromise [3, 4]. Whilst a spinal fusion is able to correct the deformity, doing this in the growing spine arrests all further growth, which limits pulmonary function even more [5]. In addition, continued anterior spinal growth after posterior fusion may result in worsening of the curve, a phenomenon known as crankshafting [6]. To circumvent these problems, “growth-friendly” techniques have been developed, which control curve progression while allowing for the spine and trunk to grow. Currently, the most common “growth-friendly” systems are the traditional growing rod (TGR) and the magnetically controlled growing rod (MCGR) [7, 8]. While both systems can control the scoliotic deformity, they have important limitations. For the TGR, the most obvious limitation is the need for repetitive surgical lengthenings (generally every 6 months), which exposes patients to high anesthetic stress at a young age, which may negatively influence neurodevelopment [9]. For the MCGR, lengthenings are non-invasive, but they still require patients to come to the outpatient clinic on a regular basis, more often than in TGR, which imposes a psychological burden on these patients and their parents [10]. In addition, both TGR and MCGR have a high mechanical (i.e. implant-related) complication rate which results in reoperations and diminished length gain [11–16]. The high rate of MCGR dysfunction recently resulted in a temporary suspension of CE certification and the advice to limit MCGR implantation in several countries [17, 18]. To overcome these limitations, two new systems were developed: the Spring Distraction System (SDS), which uses a compressed spring around standard rods to generate distraction, and the One Way Self-Expanding Rod (OWSER, CE-marked as Nemost®; Euros, SAS, La Ciotat, France), which is a one-way sliding rod with split retaining ring system. Both systems are designed to facilitate growth of the spine without interventions, while maintaining curve correction. Previous publications have shown the feasibility of both systems [19, 20]. However, patient populations and surgical strategies were heterogeneous, and the case series design could have led to selection bias. To determine clinical efficacy, identify early mechanical failures, and to generate level 1 evidence for potential differences between the techniques, a single-blinded, prospective randomized trial was considered the ideal strategy.

## Methods

### Study aims

The primary aim of the BiPOWR trial is to prospectively describe and compare efficacy (coronal and sagittal curve maintenance) and –safety (occurrence of Serious Adverse Events; SAEs) of two innovative implant systems in neuromuscular EOS patients. Due to the relatively short follow-up of participants (1 year), with intermediate instead of final outcomes, the study is regarded as a limited-efficacy and -safety study [21]. A secondary aim is to describe and compare spinal- and implant growth, peri-operative parameters and Health-Related Quality of Life (HRQoL).

### Study design

The BiPOWR trial is a prospective, multicenter, randomized, surgical trial with two parallel groups and a 1:1 allocation ratio. Ethical approval was provided by the Institutional Review Board of the UMC Utrecht (METC 18–179). Following inclusion, patients undergo “growth-friendly” scoliosis surgery with one of two implants, the SDS or the OWSER. Which implant they receive is decided by randomization. Following implantation, the patients are followed until 12 months post-operatively, during which their radiographic- and clinical outcomes will be described and compared. The analysis at 12 months provides a point for interim analysis in the short follow-up, to determine whether one or both implants show short-term technical malfunctions, and to ascertain whether early detectable differences are present in other outcome domains. After the 1 year analysis, both patient cohorts are followed bi-yearly for several more years, until after skeletal maturity, to show efficacy and safety in the long-term. A SPIRIT table showing a detailed follow-up timeline for the first year of follow-up is shown in Table 1.

**Table 1 Tab1:** SPIRIT table

	**STUDY PERIOD**							
	**Enrolment**	**Allocation**	**Surgery**	**Post-allocation**				
**TIMEPOINT****	***-t***_***2***_ Before -2 weeks	***-t***_***1***_ -2 weeks	***t***_***0***_ Day of surgery	***t***_***1***_ + 1 week	***t***_***2***_ + 4 weeks	***t***_***3***_ 3 months	***t***_***4***_ 6 months	***t***_***5***_ 12 months
**Enrolment**								
Eligibility screen	X							
Informed consent	X							
Allocation		X						
**Interventions**								
Spring Distraction System			**Implant in Situ**	**Implant in Situ**	**Implant in Situ**	**Implant in Situ**	**Implant in Situ**	**Implant in Situ**
One Way Self-Expanding Rod			**Implant in Situ**	**Implant in Situ**	**Implant in Situ**	**Implant in Situ**	**Implant in Situ**	**Implant in Situ**
**Outcomes**								
Main coronal Cobb angle	X			X	X	X	X	X
Serious Adverse Events			X	X	X	X	X	X
Implant length				X	X	X	X	X
EOSQ-24 questionnaire	X			X	X	X	X	X

### Eligibility criteria

Inclusion criteria are:Neuromuscular or syndromic EOS (i.e. diagnosis before age 10).Progressive EOS with an indication for bipolar fixation extending to the pelvis.Non-ambulant patients.Age < 12 years.

Exclusion criteria are:Closed triradiate cartilage.Main curve proximal end vertebra at or above T3.Presence of skeletal dysplasia affecting growth.Presence of disease that severely influences bone quality or is associated with soft tissue weakness.Presence of active systemic disease (other than neuromuscular disease).Congenital spinal anomaly of  > 5 vertebrae.Previous instrumented spinal surgery.Patients who cannot be followed for 1 year post-operatively.

### Recruitment and informed consent

The treating physician identifies potential eligible patients, and asks the patient and their caregiver(s) whether they would like to receive additional study information. Upon agreement, the principal investigator is consulted for approval and the research team subsequently sends the study information. After at least two weeks, a consultation with the research team takes place where the in- and exclusion criteria are assessed, the study is explained in detail and patients’ questions are answered. Care is taken to ensure that the study design (in particular blinding and randomization) and the similarities and differences of the two treatment arms are understood. If willing to participate, the informed consent form is signed in duplicate and the consent is noted in the electronic patient record.

### Randomization and blinding

After inclusion, the patient is randomized into one of two treatment groups. Before the start of the trial, a randomization sequence was created using a computer-generated random number sequence, which was used to create a permuted block design with random block sizes. A random number of blocks with random block sizes of 2, 4, 6 and 8 created the final sequence containing 28 randomized patients. The sequence was converted into allocation notes, which were stored in opaque, sealed envelopes. Each allocation envelope was sealed into a second, sequentially numbered, opaque envelope. The use of two envelopes prevents the use of trans-illumination to unblind allocation. Two weeks before surgery, the next numbered study envelope is retrieved by two members of the study team. The envelopes, the seals in particular, are visibly examined for tampering. The allocation is confirmed by both research team members, and the pseudonymized patient number is written on the allocation note and the study envelopes. The treating physician is then notified of the outcome of the allocation, to order the required implants.

The patient and caregiver(s) remain blinded to the result of allocation until after surgery to prevent selection bias through termination from the study before surgery commences, which is a possibility if they have a strong preference for one treatment arm [22]. After surgery has taken place, the allocation outcome is shared with the patient and caregiver(s). While blinding patients during the entire study period is theoretically possible, enforcing this would require extreme effort, as it would preclude the treating physician of showing any of the follow-up radiographs to the patient and caregiver(s) as these clearly show the different implants. Since these radiographs often provide a wealth of information to the patient and caregiver(s), denying them these raises ethical concerns and would likely decrease enrolment rate.

### Surgical procedure and treatment arms

All surgical procedures will be performed using a less invasive bipolar posterior approach with somatosensory and motor-evoked potential monitoring [23]. The distal anchor is created with iliosacral screws (Tanit®; Euros, SAS, La Ciotat, France). The proximal anchor for SDS consists of bilateral pedicle screws at 3 consecutive levels, typically T2-T4. For the OWSER, a series of laminar- and pedicle hooks spanning 5 vertebrae is applied (T2-T6).

The SDS (Fig. 1) is an adjunct to standard 5.5 mm cobalt-chromium (CoCr) rods. It consists of three components: (1) a titanium (Ti6Al4V) spring placed over the rod, (2) two stacked oversized parallel connectors and (3) a buttress used to tension the springs (Stryker, Leesburg, VI, USA). In neuromuscular EOS, the SDS is placed bilaterally. The concave rod receives a strong 100 N spring (spring constant (*k*) = 1.32 N/mm), the convex rod receives a weaker 50 N spring (*k* = 0.68 N/mm). Around 6–7 cm of residual rod length is left for growth. The parallel connectors are secured to the distal anchor rods and the rod containing the spring is allowed to slide in the connector.

**Fig. 1 Fig1:**
[figure not shown]
Spring Distraction System. The SDS consists of three components that are added to standard growing rods. It provides a continuous distraction force during follow-up, without the need for repeated lengthenings. In the BiPOWR trial, the distal anchors are iliosacral screws instead of pedicle screws. Green: A side-to-side connector with one oversized hole through which a CoCr rod can slide freely. Gold: Ti6Al4V springs which can be compressed over the rod. Blue: The buttress compresses the spring against the side-to-side connector

The OWSER (Fig. 2) consists of two titanium components: (1) a 5.5 mm titanium long rod with a notched end, and (2) a sliding domino that passively migrates only one way across the notched rod segment. The long rod is connected to the proximal anchor with the notched end facing distally. The connector is fixated with a short rod to the distal anchor. Implant growth potential (i.e. the notched segment of the long rod) can be 50 or 80 mm. In neuromuscular EOS, the OWSER is also placed bilaterally.

**Fig. 2 Fig2:**
[figure not shown]
One Way Self-Expanding Rod. The OWSER is a growing rod that passively lengthens one way as the spine grows. In the BiPOWR trial, the distal anchors are iliosacral screws instead of pedicle screws. Blue: The proximal fixation consists of hooks positioned in a claw configuration. Two crosslinks are added for torsional stability (green). Red: The growing domino, combined with a rod that is serrated across its distal length, allows for lengthening. The reserve length can be 50 mm or 80 mm long. Movement in the other direction is prevented by a split retaining ring system inside the domino

The implant configurations are shown radiographically in Fig. 3. All patients treated by either SDS or OWSER are allowed unrestricted physical activities postoperatively. We do not routinely perform manual axial trunk traction in the outpatient clinic for these most vulnerable of OWSER patients. For OWSER implant lengthening, we instead rely only on passive lengthening due to spinal growth, in combination with normal traction and bending generated through daily activities.

**Fig. 3 Fig3:**
[figure not shown]
Implant configuration. Representative implant configurations of the SDS (top) and the OWSER (bottom) are shown. Top. A proximal foundation of 3 pedicle screws is placed (blue). The distal foundation consists of iliosacral screws. CoCr rods are placed through open side-to side connectors (green). Around these rods, 2 springs (orange) are positioned, which push against these connectors and a proximal locking buttress. The gliding parts of the rods (red) become shorter as the spine grows. Bottom: Here, the proximal foundation consists of 2 claws (blue), created with hooks. The distal foundation consists of iliosacral screws. The Ti6Al4V OWSER rods are inserted with the dominos placed distally (purple). The notched part of the rods (red) can only lengthen one-way through the domino’s

### Outcomes

The primary outcomes include coronal Cobb angle – measured on radiographs – and occurrence of SAEs (defined as unplanned medical events which (could) result in permanent disability/damage, or which requires (lengthening of) hospitalization, a re-operation, or inpatient medical managing). SAEs will be categorized as either device/surgery related (e.g. rod fracture, post-operative neurological deficit), or as disease-related (e.g. pneumonia, pain) according to a previously created complication classification system for use in EOS treatment [24]. In addition to SAEs, complications that do not meet the criteria for an SAE, but which are device/surgery related (e.g. superficial infections, proximal junctional kyphosis) will also be recorded.

Secondary radiographic measurements include parameters such as T1-T12, T1-S1 and instrumented height, T5-T12 kyphosis, L1-S1 lordosis, and pelvic obliquity. In addition, implant length will be calculated at each timepoint for both groups (SDS: Spring length, OWSER: Notched rod length) so that implant growth velocity over time can be graphed and calculated. The number of outpatient axial traction events of OWSER patients, if these are performed, will also be reported. All radiographic measurements will be performed by a trained assessor. To ensure data quality, radiographic measurements are performed semi-automatically in Surgimap v2.3.2.1 software (Nemaris, New York, USA), after which all measurements are audited by the assessor. At the end of the data collection phase, all radiographic measurements are re-assessed by a second trained assessor who is blinded to the first assessors’ measurements. Measurements are compared and disputed measurements are discussed until consensus is reached. If differences are believed to be caused by random measurement variation, the arithmetic mean of both assessors’ measurement is taken.

HRQoL will be measured with the validated Dutch version of the EOSQ-24 which consists of 24 questions in 10 domains, from which a domain- and total score is calculated [25, 26]. All outcome parameters are measured pre-operatively, immediately post-operatively, and at 1, 3, 6, and 12 months follow-up.

### Sample size calculation and statistical methods

The sample size calculation is based on potential differences between groups in maintenance of the coronal curve between the post-operative situation and 1-year follow-up. A difference in Cobb angle ≥ 5˚ is considered clinically relevant and can be reliably measured [27]. In our previous MCGR cohort studies, we found a change in Cobb angle between post-operatively and 1 year follow-up of 1˚ (SD 5.1˚) [28]. To determine differences in curve maintenance between groups ≥ 5˚ with a power (1-β) of 0.8, α = 0.05, and SD = 5.1˚, we calculated a sample size of n = 28, with a repeated measures ANOVA between factors design (comparing 2 timepoints). With an allocation ratio of 1:1, this means that 14 patients have to be included in each experimental group.

If all assumptions for performing repeated measures ANOVA are met, both systems will be compared with respect to coronal curve maintenance; age and sex will be included as covariates. For the other continuous variables, repeated measures ANOVA will be used, with the same covariates, but including all evaluated time points. If the assumptions for performing repeated measures ANOVA are not met (e.g. due to missing data), repeated measurement multilevel modelling will instead be performed, with patient, age, sex and treatment group as level 2 variables, and follow-up time as a level 1 variable.

A Kaplan–Meier survival analysis will be performed comparing both groups. The survival curves showing SAE-free survival of both groups will be statistically compared with the Log-Rank test. Analysis of EOSQ-24 scores will be performed using repeated measures ANOVA. In case there are missing EOSQ-24 item scores or questionnaires, multiple imputation with parcel summary scores will be performed using a previously published statistical method [29]. For all statistical tests, statistical significance will be set at *p* < 0.05. All statistical analyses will be performed in IBM SPSS statistics v.26.0.0.1 (Chicago, USA).

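### The only specified Cobb contrast measures loss after surgery and ignores correction achieved at surgery, so a maintenance result alone cannot show which implant leaves the smaller curve at 12 months

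*Protocol article*

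**What the plan says.** In the protocol article, 'Sample size calculation and statistical methods' bases the trial on "potential differences between groups in maintenance of the coronal curve between the post-operative situation and 1-year follow-up". It compares two timepoints by repeated measures ANOVA, and "age and sex will be included as covariates". A 5-degree difference "is considered clinically relevant and can be reliably measured". The SD comes from an earlier cohort treated with magnetically controlled rods, in which "we found a change in Cobb angle between post-operatively and 1 year follow-up of 1˚ (SD 5.1" degrees). The multilevel model held in reserve also lists age and sex but no pre-operative Cobb.

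Three other places bear on this:

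- 'Randomization and blinding' opens the allocation two weeks before surgery. The post-operative film therefore follows both allocation and implantation.
- 'Surgical procedure and treatment arms' describes arms that differ in construct. "The proximal anchor for SDS consists of bilateral pedicle screws at 3 consecutive levels, typically T2-T4", whereas the OWSER has hooks spanning five vertebrae. The rods are cobalt-chromium in one arm and titanium in the other, and the springs distract actively whereas the OWSER lengthens passively.
- Table 1 marks "Main coronal Cobb angle" at enrolment as well as at every post-operative visit, and 'Outcomes' confirms a pre-operative measurement.

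Use of all time points is specified only for the remaining variables: "For the other continuous variables, repeated measures ANOVA will be used, with the same covariates, but including all evaluated time points". No contrast is named for initial Cobb correction or for Cobb at 12 months.

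**The concern.** For each child, net change from pre-operative to 12 months is the correction at surgery plus the later loss. The primary contrast sees only the second term. Because the implants differ in anchors, rods and distraction, the first term may also differ by arm, and it belongs to what the implant does for the patient.

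At stake is how the result will be read. The article names coronal Cobb angle as a primary outcome and describes the trial as determining limited efficacy. A significant difference in maintenance would easily be taken to mean better curve control, although the arm that lost more could still have the straighter spine at 12 months. The limitations listed in the Discussion do not warn of this.

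**Working it through.** **1. The plan's own figure.** The article states "with a power (1-β) of 0.8, α = 0.05, and SD = 5.1˚, we calculated a sample size of n = 28". Inputs: difference 5, SD 5.1, two groups, m = 2 timepoints. Effect size f = 5/(2 × 5.1) = 0.490. For the between-factors test, λ = f² × N × m/(1 + (m − 1)ρ). With ρ = 0.5 (assumed; the article gives none) and N = 28, λ = 0.2403 × 28 × 2/1.5 = 8.97 and power is 0.822; N = 26 gives 0.791. So 28 is reproduced under that assumption.

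**2. Power of the contrast named as primary.** SD 5.1 is the SD of the change. A two-sided t test on the change with 14 per arm has noncentrality 5/(5.1 × √(2/14)) = 2.594 on 26 degrees of freedom, so power is 0.704. This is the reference for the cost of a covariate below. Whether 28 is enough is a separate question.

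**3. Can maintenance and 12-month Cobb point in opposite directions?** An example with assumed values: 60 degrees pre-operatively in both arms, and each arm relapsing by 20% of its correction.

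| | Post-op | Correction | Loss (20%) | 12 months |
|---|---|---|---|---|
| Arm A | 30 | 30 | 6 | 36 |
| Arm B | 40 | 20 | 4 | 44 |

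Maintenance favours B by 6 − 4 = 2 degrees. The 12-month Cobb favours A by 44 − 36 = 8 degrees. The directions can differ, but 2 degrees is below the 5-degree threshold, and the power to detect it at 14 per arm is about 0.17. Under the same relapse rule, a 5-degree difference in loss needs a 5/0.2 = 25-degree difference in initial correction.

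**4. Can the change analysis tell the cases apart?** Simulation with 14 per arm, 4,000 runs per case and change SD 5.1. Implant A loses 5 degrees more than B (6 v 1). Assumed: pre-operative mean 70 and SD 15, slope of post-operative on pre-operative Cobb 0.55, residual post-operative SD 8.

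| A's extra initial correction | A's net advantage at 12 months | Change analysis: A significantly worse | 12-month Cobb adjusted for pre-op: A significantly better |
|---|---|---|---|
| 15 | +10 | 71% | 76% |
| 10 | +5 | 71% | 25% |
| 5 | 0 | 70% | 2% |
| 0 | −5 | 70% | 0.1% |

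The change analysis gives the same answer in all four cases, as it must, because initial correction cancels out of it.

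**5. What the pre-operative Cobb does as a covariate.** Simulating the example in step 3 (same slope and SDs) gives a mean difference in loss of 2.0 degrees both with and without it: randomisation balances it, so the expected difference does not move. It can only add precision. With SD × √(1 − r²) and one degree of freedom spent, where r is the correlation of pre-operative Cobb with the post-operative change, power at 5 degrees is 0.703 at r = 0, 0.707 at 0.1 and 0.721 at 0.2, against 0.704 unadjusted. The article gives no r.

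**6. Precision of a 12-month contrast.** This needs the SD of 12-month Cobb and its correlation with the pre-operative value; the article gives neither. Over assumed correlations of 0.5 to 0.8, power for 5 degrees at 14 per arm (normal approximation) is 0.48 to 0.79 at SD 8, 0.33 to 0.60 at SD 10 and 0.17 to 0.31 at SD 15.

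**The case against.** The strongest reply is that maintenance is the declared aim. The Abstract and 'Study aims' say so, and the Background describes both systems as meant to hold correction while the spine grows. The Discussion presents the one-year endpoint as a look at early mechanical failure and short-term efficacy, and the findings as an initial indication only. Loss after surgery fits that question. This stands, and is why maintenance should remain primary.

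The Abstract also promises that all outcomes will be compared between groups, and a fuller protocol exists, so supportive Cobb contrasts may be planned there. That lowers the weight of the point. It does not remove it, because the article does fix the primary contrast and its covariates.

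The sample size is labelled a between-factors design. If the group main effect over the two post-operative films were the test, greater correction would be credited rather than penalised. The text, however, names curve maintenance as what is compared.

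A reader might infer several stronger things that the document does not support:

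- *That the comparison has lost the protection of randomisation.* It has not. Both films are post-randomisation outcomes, and their difference can be compared across the randomised arms. Conditioning on the post-operative Cobb would raise that problem, and the plan does not do so.
- *That leaving out pre-operative Cobb causes the problem.* Step 5 shows that the covariate leaves the expected difference in loss unchanged.
- *That a material power gain is being given up.* Reaching 0.74 to 0.82 would need r of 0.3 to 0.5 with the change, and nothing in the article supports that.
- *That including the pre-operative visit dilutes the group effect for the other outcomes.* This presumes a test of the group main effect. The article does not say which term is tested, a group-by-time test would use that visit as its reference, and implant length has no pre-operative value in Table 1.

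**Conclusion.** The point holds as one of interpretation. The specified Cobb contrast answers which implant loses less correction after surgery. It does not answer which implant leaves the smaller curve at one year, and no other Cobb contrast is specified to cover that.

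The size cannot be given, since no document reports initial correction by implant. If both implants correct equally, maintenance and net control agree and nothing is distorted. The relapse example yields only 2 degrees on the primary contrast, and its losses of 6 and 4 degrees are well above the only documented mean change, 1 degree. A reader might infer that the trial is likely to prefer the wrong implant; the document shows only that it could not recognise such a case from the maintenance result alone. That conclusion needs no assumed figure, because it follows from the definition of the contrast. Every numerical illustration rests on the assumptions stated with it.

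**What to change.** In the analysis plan:

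1. Keep change from post-operative to 12 months as the primary Cobb contrast.
2. Add pre-operative Cobb to age and sex as a covariate, for precision only, and state that it does not settle the interpretation.
3. Fit post-operative and 12-month Cobb jointly with a group-by-visit term. Pre-specify two supportive contrasts by arm, with confidence intervals and both adjusted for pre-operative Cobb: initial correction and Cobb at 12 months.
4. Word the primary conclusion as one about maintenance. Make no claim of better curve control or efficacy if the adjusted 12-month contrast points the other way.

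No new data are needed. The covariate costs one degree of freedom: power at 5 degrees goes from 0.704 to 0.703 if it explains nothing. The 12-month contrast will probably be imprecise with 28 patients, so it should be labelled a check on direction and not a second powered comparison.

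### The 80% power is not delivered: n = 28 comes from a between-factors formula, and 14 per arm give about 70% power for the difference in Cobb change that the trial targets

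*Protocol article*

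**What the plan says.** All of the following is in the protocol article, Sample size calculation and statistical methods, unless noted.

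- The quantity powered is "potential differences between groups in maintenance of the coronal curve between the post-operative situation and 1-year follow-up".
- The target is on that scale: "To determine differences in curve maintenance between groups ≥ 5" degrees.
- The SD is on that scale too. In the group's earlier cohort of magnetically controlled rods, "we found a change in Cobb angle between post-operatively and 1 year follow-up of 1˚ (SD 5.1" degrees).
- The calculation uses "power (1-β) of 0.8, α = 0.05, and SD = 5.1" degrees, and reaches n = 28 "with a repeated measures ANOVA between factors design (comparing 2 timepoints"). No correlation between the time points is given, and no one-sided test is mentioned.
- With 1:1 allocation, "this means that 14 patients have to be included in each experimental group".
- The planned analysis of curve maintenance is repeated measures ANOVA with age and sex as covariates, at p < 0.05.
- Under Randomization and blinding, the blocks "created the final sequence containing 28 randomized patients".

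**The concern.** Effect and SD are both stated for the change between two time points. With two groups and two time points, a difference in change is the group-by-time interaction, and its test is the same as a two-sample t-test on each patient's change. The between-factors test in a repeated measures ANOVA is the group main effect: it compares the groups on the mean of the two readings. Its variance is reduced because two readings are averaged. A change score has already used both readings, so applying that reduction to an SD of change counts a gain that is not there.

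Curve maintenance is the only endpoint for which the article gives a sample size basis. If the stated power is too high, a true 5° difference is more likely to be missed than readers are told, and a non-significant result carries less weight than it appears to.

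**Working it through.** **Inputs.** From the sample size section: difference δ = 5°, SD of change σ = 5.1°, α = 0.05, power 0.80, 2 time points, 14 per arm. Assumed: a two-sided test, because an ANOVA F test is planned and no direction is given; and a correlation ρ between the two readings, needed only in step 1.

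**1. Reproducing n = 28.** For the between-factors test with m = 2 measurements:

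- f = δ/(2σ) = 5/10.2 = 0.490
- λ = f² × N × m / (1 + (m − 1)ρ), tested on F(1, N − 2)

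At ρ = 0.5:

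- N = 26: λ = 0.2403 × 52/1.5 = 8.33, power 0.791
- N = 28: λ = 0.2403 × 56/1.5 = 8.97, power 0.822

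So 28 is the smallest even total that reaches 80%. The result varies with the assumed correlation:

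| ρ | smallest even N for 80% |
|---|---|
| 0 | 20 |
| 0.4 | 26 |
| 0.5 | 28 |
| 0.6 | 30 |
| 0.8 | 32 |
| 1.0 | 36 |

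A value of 0.55 also gives 28 (0.778 at N = 26, 0.810 at N = 28). The stated 28 is thus consistent with the named formula at a correlation near 0.5.

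**2. Power for the difference in change.** Two-sample t-test on change scores, noncentral t with 26 df:

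- d = 5/5.1 = 0.980
- standard error = 5.1 × √(2/14) = 1.928°
- noncentrality = 5/1.928 = 2.594
- power = **0.704**

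Losing 2 df to age and sex, with no variance explained, gives 0.702. The normal approximation gives 0.737. The between-factors formula at ρ = 1, where averaging brings no gain, also returns 0.704.

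**3. What 80% would take.**

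| per arm | power for 5° |
|---|---|
| 12 | 0.631 |
| 13 | 0.670 |
| 14 | 0.704 |
| 17 | 0.792 |
| 18 | 0.815 |

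That is 18 per arm, 36 in total. With 14 per arm, 80% is reached for a difference of 5.61°, or for 5° if the SD of change is 4.55°.

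**4. Expected precision.** 95% confidence interval half-width = t(0.975, 26) × 1.928 = 2.056 × 1.928 = 3.96°.

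**5. If the group main effect were itself the test used.** Suppose the groups are equal after surgery and differ by 5° only at 1 year. The difference in the average of the two readings is then 2.5°. With the SD of change held at 5.1°, power at 14 per arm is about 0.30 if ρ = 0.5 and 0.13 if ρ = 0.8. This test would not answer the stated question.

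**The case against.** - **The correlation is inferred.** True: the article does not give it, and more than one value returns 28. This limits only the account of where 28 came from. The 0.704 uses only the stated 5°, 5.1°, 0.05 and 14 per arm, with a two-sided test.
- **A one-sided t-test also gives 14 per arm** (0.811; 0.783 at 13). The article names a repeated measures ANOVA, states no direction, and plans an ANOVA comparison at p < 0.05. This route is not the one described.
- **Age and sex may sharpen the comparison.** This stands as a condition. If they explained 10% of the variance in change, power would be about 0.75. To reach 80% they would have to explain about 21%, since 1 − (4.545/5.1)² = 0.206. The article claims no such gain, so 70% should be stated as the figure before any gain.
- **Losses may be few.** Patients who cannot be followed for 1 year are excluded, and multilevel modelling is planned if data are missing. An article may also leave an attrition allowance to the full protocol. The figures for 13 and 12 per arm therefore describe a case in which lost patients contribute nothing; they are not a forecast, and the finding does not rest on them.
- **The trial calls itself limited-efficacy**, and its Discussion treats the results as an initial indication that needs confirmation. That lowers the risk of over-reading a null result. It does not make the stated power correct.

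**Conclusion.** The concern holds; the power statement is wrong as written. The calculation is internally reproducible, but it answers a different question from the one posed: a formula for the average of two readings was applied to an effect and an SD defined on their difference. For the difference in curve maintenance, 28 patients give 70% power rather than 80%, a shortfall of about 10 percentage points. Put another way, the trial is 8 patients short of 80% power at 5° (36 against 28), or has 80% power at 5.6°, above the 5° the article calls clinically relevant.

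This rests on a two-sided 0.05 test, on 5.1° being the SD of change as the article reports it, on that SD carrying over from the earlier cohort to the two new implants, on all 28 being evaluable, and on no gain from the covariates.

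**What to change.** In the sample size section, replace the power statement with wording such as:

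> The comparison is the group-by-time contrast, that is, the between-group difference in Cobb change from the post-operative reading to 1 year. With an SD of change of 5.1° and a two-sided α of 0.05, 28 evaluable patients give 70% power for a difference of 5° and 80% power for 5.6°, before any gain from adjusting for age and sex. If lost patients contribute no data, power for 5° is 67% with 26 evaluable and 63% with 24. The expected 95% confidence interval half-width is about 4°. A non-significant result will be taken to exclude a 5° difference only if the interval does so.

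Remove the reference to the between-factors design, and state in the analysis paragraph that the group-by-time term is the test of curve maintenance.

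The cost is wording only. The sample size, randomization list and trial conduct stay as they are; the stated power becomes less favourable.
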